### 2.5 Outcome parameters

#### 2.5.1 Primary outcomes

The feasibility of the eccentric training program in people with low back pain and MS is evaluated by means of quantitative and qualitative measures in regard to the practical aspects of study conduction, the measurement setup and procedure and the performance of the intervention program. To evaluate the study process, recruitment rate, retention and drop-out rates will be assessed. Compliance and adherence of the participants to the eccentric exercise program are based on the training log, detailing a) how many sessions are done per week, b) which exercises are performed, c) at which intensity is trained (RPE via Borg Scale) and d) whether exercises are modified. Adverse events throughout the intervention period are documented to evaluate the safety of the program. Additionally, a subjective rating (5-point Likert-Scale) of the participants on the question whether the exercise program can be realized in a good manner regarding the exercise selection, the required time and materials is used to evaluate the feasibility of the implementation.

#### 2.5.2 Secondary outcomes

Besides the primary outcomes on study feasibility, additional surrogate parameters, such as preliminary assessments of possible intervention effects on overall health status, mobility, and postural control as well as muscle strength, are derived. Changes in the surrogates from baseline to follow-up assessment are considered and form the basis for future multi-center investigations on the efficacy of the eccentric training program. Further, the amount and type of missing data in the specific population groups are evaluated to identify possible bias during the measurement and intervention procedure. All outcome parameters are listed in **Table 1**.

**Table 1 pone.0270875.t001:** Feasibility and surrogate outcomes of the pilot intervention study.

Feasibility Outcomes	Surrogate Outcomes
**Study process:** • recruitment rate • retention rate • drop-out rate **Compliance and adherence:** • performed sessions [N] • adaptations to exercise selection and exercise modification [comments] • exercise intensity: RPE [Borg scale; 6–20] **Safety:** • adverse events [N] • pain [NRS, 0–10] • muscle soreness [NRS, 0–10] **Program evaluation:** • exercises, time, material [5-point Likert-scale]	**Questionnaires:** • EQ-5D • CPG (only LBP) • SF-36, MSWS-12, MFIS, FES-I (only PwMS) **Mobility:** • TuG [s]; 5-STS [s] • 2min-walk test [m] (only PwMS) **Postural Control:** • COP sway length [mm] for bi- & uni-pedal stance **Strength:** • peak torque [Nm] knee flex/ext • peak torque [Nm] trunk flex/ext (only LBP) **Blood Samples:** • creatine kinase • myoglobin • C-reactive protein • interleukins (IL-6, IL-8, IL-10, IL-1β, IL-1ra, IL-4) • tumor necrosis factor-alpha

RPE: rating of perceived exertion; NRS: numeric rating scale; EQ-5D: Questionnaire developed by the EuroQol Research Foundation to assess health status; TuG: Timed Up and Go test; 5-STS: Five-times Sit-to-Stand test; CPG: Chronic Pain Grade questionnaire; SF-36: Short Form 36 Health Survey; MSWS-12: 12-item Multiple Sclerosis Walking Scale; MFIS: Modified Fatigue Impact Scale; FES-1: Falls Efficacy Scale–International.

### 2.6 Dta management and statistics

Identifying data of the participants will be recorded once after their inclusion into the study and kept separately from all other study documents. The collected data will be pseudonymized. Documentation and storage of the measurement data takes place on password-protected, department/clinic-internal computers as well as on a web-based documentation form in accordance with the applicable data protection regulations of both countries. All study documents are locked at all times in office spaces only accessible to study team members.

Data of feasibility and surrogate outcomes are analyzed descriptively considering measures of frequency, central tendency, and distribution. The eccentric intervention program will be considered feasible when 70% of the participants adhered to two-third of the training sessions and performed the second measurement after the intervention period [59–62]. To allow conclusions about the potential efficacy of the intervention program only participants that adhered to prescriptions of the exercise program are included in the comparison of baseline and follow-up assessments. Prior to any data analysis plausibility and range checks will be carried out. A per protocol approach is used in the pilot investigation even though an intention-to-treat approach will be preferred for future investigations on the effectiveness of eccentric exercise programs. Possible intervention effects on: patient reported outcomes, mobility, postural control, strength, and muscle-metabolism as well as inflammatory markers are tested by a two-way repeated measures ANOVA (within factor: time, between factor: group allocation). If the variance analysis indicates interaction effects, post hoc testing with respective Bonferroni correction is applied to identify group differences depending on measurement time points. Effect sizes associated with univariate F-statistics will be expressed as eta-squared (η^2^) and effect sizes based on a difference in mean scores will be expressed as Cohen’s d. Study results are planned to be communicated via peer-reviewed international journal publications.

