### 2.4. Assessments/Procedure

#### 2.4.1 Experimental procedure

Potential participants learn of this study through personal contact, e-mails and printed advertisements posted at the two centers. The study team’s contact details are provided to enable interested participants to further enquire and participate in the study. Interested participants are provided with an information pack describing the study, supported by verbal information. They are screened for eligibility according to the pre-specified inclusion and exclusion criteria at the above-mentioned study sites. With inclusion criteria met, written informed consent of the participants are obtained. Group assignment is randomly performed where applicable by the principal investigators based on a generated list matched by age and gender. The randomization list is kept concealed (password protected, exclusively accessed by principal investigator) until intervention assignment. Only data analysts remain blinded to group allocation. Prior to the baseline measurement, participants undergo a physical examination (self-reported anamneses: verified diagnosis; current pain level, complaints and impairments; musculoskeletal/orthopedic examination) by a physician to rule out contraindications that restrict or prevent participation in regard to testing and exercise intervention. Baseline measurements (M1) are conducted three days before the first training session, comprising: (1) blood sampling, (2) self-reported questionnaires, (3) mobility, (4) balance and (5) strength testing. All participants, irrespective of group allocation, perform the test battery. Additional blood sampling is conducted immediately before and three days after the first training session in order to assess the acute reaction to the initial training bout. The follow-up measurement (M2) is conducted three days after the last training session. The follow up assessment session includes tests identical to those collected at baseline, with the addition of participant rating scores of the intervention program (5-point Likert-Scale regarding exercise selection, time effort and required equipment).

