## 3. Discussion

It is of overall interest to evaluate whether eccentric exercises can be applied in clinical populations that would potentially benefit from eccentric loading specific effects. Evidence is slowly accumulating regarding the use of eccentric exercises in for example clinical populations with cardiorespiratory disease [20], chronic obstructive pulmonary disease [21], cancer [22] and obese patients [23]. However, studies are rare for orthopedic and neurological conditions even though those populations would potentially benefit from eccentric strengthening exercises. Therefore, it is the purpose of the study presented in this protocol to investigate the feasibility of a six-week eccentric exercise program in people with low back pain and MS. It might thereby form the foundation for future studies assessing the efficacy of eccentric strengthening exercises and the facilitation of eccentric training modalities in the therapy of orthopedic and neurological disorders. Often a safe application of high mechanical loads is questioned in those populations. The present study will add knowledge on the safety, practicability and initial effects regarding strength, postural control, function and mobility as well as inflammatory reactions of an eccentric strengthening program with moderate to heavy training intensities. Further, the adherence to exercise programs is vital for their effectiveness. Surveys show that a large proportion of adults do not meet recommendations on physical activity which might be due to individual limitations, such as low baseline level and inexperience with intense physical exertion, limited physical capacity or impairment and disability due to medical circumstances, limited availability of sports facilities and equipment, or economic constraints [63, 64]. The adherence to exercise therapy programs is critical for clinical outcomes in people with low back pain [65] and MS [66] as well as in patients with other clinical conditions [67]. Thus, training programs need to be targeted, efficient, and fit into daily life in order to increase adherence in the prevention and therapy of diseases [68]. The eccentric exercise program presented in this protocol may address some of the afore-mentioned obstacles and supports the adherence and compliance as the program consists of simple exercises that can be easily modified in their complexity and intensity according to the individual physical capacity of the patient. Moreover, exercises can be performed without heavy equipment (only small weights and resistance bands) which allows a conduction in both, clinical settings and home environments. Furthermore, the program presents a collection of exercises addressing different muscle groups of the trunk and lower extremity facilitating a variety during the process of exercise progression. Documentation of adherence and compliance in accordance with initial intervention effects within the present study will allow first insights into dose-response relationships and may be helpful during the development of future study programs. Even though this eccentric program is designed for the treatment of people with low back pain and MS, it contains basic exercises for the trunk and the lower extremity which may be as well beneficial for other populations, due to the unspecific nature of the selected exercises. However, the generalizability of findings especially for populations with increased impairments seem limited as only participants with mild low back pain and MS (<4.5 EDSS) are recruited in this study.

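### The only planned efficacy comparison keeps adherers alone, so the contrast between the two MS groups depends on behaviour after allocation, with no as-allocated analysis beside it

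*Protocol article*

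**What the plan says.** Section 2.6 gives a purpose and a rule. The purpose: "To allow conclusions about the potential efficacy of the intervention program". The rule: "only participants that adhered to prescriptions of the exercise program are included in the comparison of baseline and follow-up assessments". It then adds: "A per protocol approach is used in the pilot investigation even though an intention-to-treat approach will be preferred for future investigations". The test is a two-way repeated measures ANOVA with time as the within factor and allocated group as the between factor. The only numeric adherence threshold in the section belongs to the feasibility criterion (70% of participants with at least two-thirds of sessions and the second measurement done). The section does not say that this threshold also defines the analysis set.

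On allocation, section 2.4.1 says: "Group assignment is randomly performed where applicable by the principal investigators based on a generated list matched by age and gender". Section 2.2 recruits CTRL and LBP in Potsdam according to back-pain status, and both MS groups at one centre in Israel under identical criteria.

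On adherence, section 2.5.1 says: "Compliance and adherence of the participants to the eccentric exercise program are based on the training log". Section 2.3.2 gives PwMS_STD its own regimen of twelve face-to-face sessions plus daily home exercise. It also calls that regimen an exercise program, and describes no adherence record for it.

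On use of the results, section 2.5.2 intends the observed changes as the foundation for later multi-centre efficacy studies. The Discussion expects that adherence, documented together with initial effects, "will allow first insights into dose-response relationships".

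**The concern.** Membership of the analysis set is decided by what participants do after allocation, while the groups are still compared by allocation. Where allocation was random, that selection can undo the balance that randomisation provides.

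The filter is also not clearly the same in the two MS groups. A log exists for the eccentric program, and none is described for standard care. If adherence is related to how a participant fares, dropping poor adherers from one group shifts that group's mean change even when the program has no effect.

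The consequence reaches past the pilot. Its estimates are meant to inform efficacy trials for which the plan itself prefers intention-to-treat, so they would come from a different analysis set than the one they are used to plan. The same filter also takes low-attendance participants out of the change data, where they would be most useful for the dose-response description that the Discussion expects.

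**Working it through.** **1. Which contrast is affected.** CTRL and LBP differ by health status and cannot be assigned. PwMS and PwMS_STD share one source and one set of criteria. Randomisation where applicable can therefore only concern these two groups. This is an inference from sections 2.2 and 2.4.1; the article does not name the pair.

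**2. How many can be removed.** The 12 per group rests on a feasibility rationale with no power calculation, so there is no figure to reproduce, and it is not disputed here.
- Sessions: 6 weeks × 3 = 18. Two-thirds of 18 = 12.
- Criterion applied per group: 0.70 × 12 = 8.4, so at least 9 must succeed and at most 3 of 12 (25%) can fall short.
- Criterion pooled over the three eccentric groups: 0.70 × 36 = 25.2, so at least 26 must succeed and up to 10 can fall short, with no limit on how many are PwMS.

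Using two-thirds as the cut for the analysis set is an assumption.

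**3. Bias by formula.** Assume no true effect, change with SD 1, correlation r between adherence and change, the lowest adherers dropped from PwMS only, and a kept fraction k. Then bias = r × φ(z)/k, where z is the cut-off on a standard normal scale. For k = 0.75 this gives 0.127 SD at r = 0.3 and 0.212 SD at r = 0.5.

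**4. Bias by simulation at the actual size.** 20,000 trials per setting, 12 per arm, the 3 lowest adherers dropped, two-sided t-test at 0.05 (alpha is assumed). With two groups and two time points, this t-test on change is equivalent to the time-by-group interaction.

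| r | Dropped from | Bias (SD) | Type I error |
|---|---|---|---|
| 0 | PwMS only | about 0 | 5.0% |
| 0.3 | PwMS only | 0.12 | 5.8% |
| 0.5 | PwMS only | 0.20 | 7.5% |
| 0.3 | both arms | about 0 | 5.1% |
| 0.5 | both arms | about 0 | 5.6% |

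The rows for both arms assume the same rule and the same r in each arm.

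**5. Bias against imprecision.** The SE of a 9 versus 12 difference is √(1/9 + 1/12) = 0.44 SD.

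**6. Session range.** If two-thirds is the cut, attendance in the change analysis runs from 12 to 18 instead of 0 to 18. With sessions spread evenly, their SD falls from 5.5 to 2.0. Now assume that 30% attend fewer than 12 sessions, and let v be the variance of sessions among those kept divided by the variance in the full set. The SE of a linear slope grows by √(1/(0.7 × v)):
- low doses spread over 0–11: SDs 2.00 and 5.03, v = 0.158, ratio 3.0;
- low doses spread over 6–11: SDs 2.00 and 3.54, v = 0.319, ratio 2.1.

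**7. Numbers kept.** For an assumed standardised difference of 0.8 in either set, approximate power is 50% with 12 versus 12 and 44% with 9 versus 12.

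**The case against.** The strongest defence is that this is a declared pilot choice on secondary outcomes. The article states the per-protocol approach and its preference for intention-to-treat later. Recruitment, retention, adherence, adverse events and program ratings carry no adherence filter. Section 2.5.2 also plans to examine the amount and type of missing data for possible bias. All of this stands, and it rules out calling the rule a hidden contradiction or a threat to the primary outcomes. It does not supply the missing comparison: participants who were measured at follow-up but adhered poorly are excluded by rule, and no other efficacy comparison is named.

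A reader might infer four stronger things that the documents do not support.
- **That the bias certainly favours the eccentric program.** The rule refers to the exercise program, and section 2.3.2 uses that term for standard care too, so the filter may cover both groups. An operational rule for PwMS_STD may stand in the full protocol.
- **That people with pain or worsening are necessarily the ones removed.** Sections 2.3.1 and 2.3.3 allow exercises to be modified, so some of them may continue and count as adherent.
- **That dose-response is a stated aim made impossible.** It is an expectation in the Discussion. Attendance of 12 to 18 sessions, exertion ratings and modifications would still vary.
- **That 30% is the most that a feasible program could lose.** Per group it is 3 of 12; if the criterion is pooled, there is no cap for PwMS.

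It is also fair to say that 0.12 to 0.20 SD is modest beside an SE of 0.44 SD. The difference is that imprecision shows in a confidence interval and systematic selection does not.

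**Conclusion.** The point holds as a weakness in a stated rule on the secondary outcomes. The only baseline-to-follow-up comparison conditions PwMS versus PwMS_STD on adherence after allocation, and no as-allocated analysis stands beside it.

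The direction depends on how the filter is applied. A filter on PwMS only or mainly probably favours the eccentric program. A filter on both groups gives a mean bias of about zero only if the rule and the adherence-outcome link match, and with two different regimens nothing ensures this. The illustrative size is 0.12 to 0.20 SD, with type I error of 5.8% to 7.5%. It rests on 3 of 12 being dropped from PwMS alone, no true effect, and correlations of 0.3 to 0.5 that the documents do not give.

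Dose-response information is weakened and not eliminated, and only to the extent that two-thirds of sessions is in fact the cut.

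**What to change.** In section 2.6:
- Make the main PwMS versus PwMS_STD comparison all allocated participants with M2 data, analysed in their allocated group regardless of sessions attended.
- Seek M2 from participants who stop early, at the planned end of the six-week period. Section 2.4.1 ties M2 to the last training session and gives no timing for them.
- Report participants without M2 by group, since an analysis of those with M2 still leaves them out.
- Keep the per-protocol set as a labelled sensitivity analysis, with one adherence rule (the same share of prescribed sessions) for both MS groups.
- Describe dose-response over the full range of sessions attended.

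The cost is a change of wording, a session record for PwMS_STD, and some effort to obtain M2 from early stoppers. M2 is already planned for all groups. Estimated effects will probably be somewhat smaller.

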### 2.2. Participants

The study is performed at two study centers, one in Germany and one in Israel. Participants of the CTRL and LBP group are recruited via the University Outpatient Clinic of the University of Potsdam, Germany. Participants with MS are recruited within the Multiple Sclerosis Center, Sheba Medical Center, Tel Hashomer, Israel. For the rational of a feasibility study a sample size of 12 participants per group is intended [43]. Participants (all sexes) aged between 18 and 65 years are included into this study. Participants eligible for CTRL group are healthy asymptomatic adults, with absence of any acute or chronic LBP. Asymptomatic participants with acute infections, pregnancy, or structural changes of the spine with or without neurological signs contra-indicating physical activities are excluded. Participants eligible for the LBP group need to report a minimum of 3 low back pain episodes within the last 12 month (not exclusively within the last 3 month) and report an average pain score of 3 or above on the numeric rating scale (NRS) within the last 3 months (NRS: numeric rating scale; 0: no pain; 10: worst imaginable pain). People with acute low back pain which occurred for the first time within the last 7 days, acute infections, pregnancy, or structural changes of the spine, with or without neurological signs contra-indicating physical activities are excluded. Participants eligible for PwMS and PwMS_STD_ group need a neurologist-confirmed diagnosis of definite MS according to the revised McDonald criteria, a score of <4.5 on the Expanded Disability Status Scale (EDSS), the ability to walk an equivalent of at least 500m without a walking aid and to be relapse-free for at least 90 days prior to testing. People with MS with cardiovascular disorders, respiratory diseases, the use of steroids or fampridine or other conditions contra-indicating physical activities are excluded.

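### For the randomisable MS contrast on outcomes measured at M1 and M2, the planned repeated-measures ANOVA is a valid but usually less precise change-score test; ANCOVA on the M1 value would normally do better

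*Protocol article*

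**What the plan says.** Section 2.6 of the protocol article names one model for all surrogate outcomes. Patient-reported outcomes, mobility, postural control, strength, muscle metabolism and "inflammatory markers are tested by a two-way repeated measures ANOVA (within factor: time, between factor: group allocation"). No covariate is named. The next step is conditional: "If the variance analysis indicates interaction effects, post hoc testing with respective Bonferroni correction is applied". The effect sizes named are eta-squared and Cohen's d, and the analysis set is per protocol.

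Four features of the design bear on this model:

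- **Assignment (2.4.1).** "Group assignment is randomly performed where applicable by the principal investigators based on a generated list matched by age and gender".
- **Groups (2.2).** "Participants of the CTRL and LBP group are recruited via the University Outpatient Clinic of the University of Potsdam, Germany", whereas both MS groups come from the centre in Israel. CTRL and LBP are defined by health status, so random assignment can only concern PwMS versus PwMS_STD.
- **Time points (2.4.1).** For most outcomes there are two, M1 and M2: "The follow up assessment session includes tests identical to those collected at baseline". Blood is the exception: "Additional blood sampling is conducted immediately before and three days after the first training session in order to assess the acute reaction". That makes four blood samples.
- **Size (2.2).** "For the rational of a feasibility study a sample size of 12 participants per group is intended".

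Section 2.5.2 makes these outcomes secondary and preliminary, but intends the observed changes to underpin later multi-centre efficacy trials.

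**The concern.** With two time points, a group-by-time interaction carries no more information than a comparison of M2 minus M1. A change score treats the baseline slope as 1. If the true slope is lower, as it is whenever the SDs at M1 and M2 are equal and r is below 1, a chance baseline difference between randomised arms is over-corrected.

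With 12 per arm such differences are not small. The standard error of the baseline gap is √(2/12) = 0.41 SD. A gap of that size at r = 0.5 shifts the change-score estimate by (1 − 0.5) × 0.41 = 0.20 SD. The shifts average out over repeated randomisations, so they are not bias, but they add noise to the one contrast with a concurrent standard-care comparator. The M1 value that would remove this noise is already collected.

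**Working it through.** **Inputs.** From the documents: n = 12 per arm, so N = 24 for PwMS versus PwMS_STD; two time points; no covariate. Assumed, because the documents give no values: r from 0.3 to 0.95, equal SDs (σ) at M1 and M2, two-sided alpha of 0.05, and a true difference of 0.8 SD for the power illustration. The 12 per group rests on a feasibility rationale without power, alpha or SD, so there is no stated figure to reproduce.

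**Step 1: the identity.** Let Δ be the difference in mean change and s² the pooled variance of the change scores.

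- Interaction sum of squares: nΔ²/4, on 1 df.
- Error mean square: s²/2, on 2n − 2 df.
- F = (nΔ²/4)/(s²/2) = Δ²/(s² × 2/n) = t².

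On one simulated data set of 2 × 12 subjects, F and t² were both 0.06265. For the MS-specific questionnaires and the walk test, which only the two MS groups have, this is the whole test. For outcomes shared by all four groups, the interaction is a one-way ANOVA on change with 3 numerator df, and PwMS versus PwMS_STD is one contrast within it.

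**Step 2: variances, in units of σ² × 2/n.**

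- Change score: 2(1 − r).
- ANCOVA with p covariates: (1 − r²) × (N − 3)/(N − p − 3). The last factor is the average cost of estimating slopes from a small sample.
- Ratio: (1 + r)/2 × (N − 3)/(N − p − 3).

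At N = 24 the factor is 21/20 for baseline alone (p = 1). It is 21/18 for baseline, age and gender (p = 3), if age and gender explain nothing further and are no better balanced than by simple randomisation.

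| r | Ratio, baseline only | Ratio, baseline + age + gender | Power at 0.8 SD: change → baseline ANCOVA |
|---|---|---|---|
| 0.3 | 0.68 | 0.76 | 0.35 → 0.48 |
| 0.5 | 0.79 | 0.875 | 0.47 → 0.56 |
| 0.7 | 0.89 | 0.99 | 0.68 → 0.72 |
| 0.8 | 0.945 | 1.05 | 0.84 → 0.86 |
| 0.9 | 1.00 | 1.11 | 0.99 → 0.99 |
| 0.95 | 1.02 | 1.14 | 1.00 → 1.00 |

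Break-even is r = 2 × 20/21 − 1 = 0.90 with baseline only, and 2 × 18/21 − 1 = 0.71 with all three covariates. At r = 0.5, 12 per arm analysed by ANCOVA act like 12/0.7875 = 15.2; at r = 0.7, like 12/0.8925 = 13.4.

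**Step 3: a smaller per-protocol set.** As an illustration only, 0.70 × 12 = 8.4, so take 8 per arm (N = 16). The factors become 13/12 and 13/10, and break-even falls to r = 0.85 (baseline only) and 0.54 (three covariates).

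**Step 4: groups that are not randomised.** If two groups differ at baseline and neither changes, ANCOVA still reports a difference of (1 − r) × baseline gap. For a gap of 1 SD that is 0.5 SD at r = 0.5 and 0.3 SD at r = 0.7.

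**The case against.** The strongest reply is that nothing here is an error. Under randomisation the change-score difference is unbiased and its test is valid. The model, post hoc rule and effect sizes are stated without contradiction, the outcomes are secondary, and feasibility is judged descriptively. All of that stands. What remains is that the article fixes a particular model, and for one contrast a better one is available from the same data.

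Four stronger readings are tempting, and the documents do not support them.

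- **Age and gender.** Because the list is matched on them and the model omits them, a reader might infer that their variance inflates the error term. It largely does not: differencing M2 and M1 removes any stable effect on level. Only effects on change remain, and nothing in the article suggests that these are material. Adding both could cost precision once r passes about 0.71.
- **A larger gain.** The large-sample ratio (1 + r)/2 would suggest savings of 25%, 15% and 5% at r = 0.5, 0.7 and 0.9. At 12 per arm the baseline-only figures are 21%, 11% and nil.
- **All outcomes.** The sentence on the model also covers the blood markers. With four sampling times in the model, the interaction is not a single change-score test.
- **All groups.** ANCOVA across LBP, CTRL and the MS groups could create a difference where none exists (step 4). The change score is not inferior there.

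The per-protocol restriction also counts against ANCOVA to some extent. Exclusions shrink the set and weaken the randomised comparison on which ANCOVA relies.

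**Conclusion.** The point holds for PwMS versus PwMS_STD on outcomes measured only at M1 and M2. There the planned test equals an unadjusted change-score t-test, which is valid but usually less precise than ANCOVA on the M1 value. The identity is exact. The size of the gain depends on r, which the article does not give. At 12 per arm the variance falls by about 21% at r = 0.5, 11% at 0.7 and 5% at 0.8, with no gain at about 0.9 and a loss of about 2% at 0.95. At 8 per arm the break-even r is about 0.85. These figures assume equal SDs at M1 and M2.

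This is a modest efficiency improvement to a secondary, preliminary analysis. It does not touch the feasibility criterion, the sample size or the validity of the planned test.

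**What to change.** Amend the wording of section 2.6 before the outcome data are analysed:

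- For PwMS versus PwMS_STD, on outcomes measured only at M1 and M2, analyse M2 by ANCOVA with group and the M1 value. Report the adjusted difference with a 95% CI.
- Add age and gender only where they are expected to predict change, and name those outcomes in advance.
- Keep comparisons that involve LBP or CTRL descriptive or on change scores.
- State a separate analysis for the blood markers that says which of the four sampling times enter.

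No new data are needed. The statistical cost is one degree of freedom, plus a slight loss of precision if r exceeds about 0.90 (about 0.85 with 8 per arm). The administrative cost is an amendment, which section 2.1 routes through both review boards and the registry.
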